## Abstract

**Background/Objectives:** Anorexia nervosa (AN) is marked by cognitive deficits, particularly reduced mental flexibility and weak central coherence, which may sustain the core psychopathological symptoms. While cognitive remediation therapy (CRT) has shown efficacy in improving these cognitive processes in AN, evidence on computer-based CRT remains limited. This study aims to evaluate the feasibility and efficacy of integrating computer-assisted cognitive remediation therapy (CA-CRT) into standard nutritional rehabilitation (treatment as usual, TAU) to improve the targeted cognitive and psychological parameters among inpatients with AN in a more personalized and scalable way. **Methods**: A multicenter randomized controlled trial (RCT) will be conducted. At least 54 participants with a diagnosis of AN will be recruited at each site and randomized into either the experimental or control group after initial screening. The intervention will last five weeks and include 15 individual CA-CRT sessions alongside 10 individual CR sessions, delivered in addition to standard care. The primary and secondary outcomes will be assessed at the end of the intervention to evaluate the changes in cognitive flexibility, central coherence, and psychological functioning. **Results**: Participants receiving CA-CRT are expected to develop more flexible and integrated thinking styles and achieve greater improvements in clinical outcomes compared to those receiving standard care alone, supporting a more personalized therapeutic approach. **Conclusions**: These findings would underscore the feasibility and clinical value of incorporating CA-CRT into standard inpatient treatment for AN. By specifically targeting cognitive inflexibility and poor central coherence in a scalable, individualized format, CA-CRT may enhance treatment effectiveness and support the development of patient-centered interventions tailored to the cognitive profiles of individuals with AN.

## 1. Introduction

Anorexia nervosa (AN) is a severe and chronic eating disorder characterized by a distorted perception of body size and shape and a fear of gaining weight or being fat, coupled with persistent severe food restriction [1]. It is one of the most common disorders in adolescence, with the highest mortality rates of any mental health condition [2]. The etiology of AN is multifactorial and complex [3,4], and it is often accompanied by psychological, physical, and cognitive complications [5,6]. Therefore, the treatment of AN remains a considerable clinical challenge across the lifespan. In children and adolescents, family-based treatment (FBT) is widely recognized as the first-line intervention, involving active parental participation in refeeding and behavioral restructuring, with robust evidence supporting its effectiveness in promoting weight restoration and reducing eating disorder psychopathology [7,8]. Other evidence-based approaches, such as enhanced cognitive-behavioral therapy (CBT-E), have demonstrated comparable outcomes and represent a viable alternative when FBT is not feasible or acceptable, as well as being a recommended treatment choice in adults [9].

Despite these available options, recent systematic reviews and meta-analyses consistently reported discouraging outcomes, with non-response rates ranging from 30% to 50%, high treatment dropout, and frequent relapse following weight restoration. For example, Berends et al. (2018) reported relapse rates of approximately 31% within 1–2 years [10], while Frostad et al. (2022) found that nearly half of patients relapsed within 12 months post-discharge [11]. A 2024 meta-analysis by de Rijk et al. confirmed a mean relapse rate of 37% over an average follow-up of 31 months, identifying a lower post-treatment BMI and higher baseline depression as significant predictors of relapse [12]. Similarly, a rapid review by Miskovic-Wheatley et al. (2023) reported relapse rates ranging from 41% at the 1-year follow-up to 30% at 22 years [13]. These findings underscore the urgent need for novel, adjunctive treatment strategies that address not only the core maintaining mechanisms of AN—such as weight restoration and disordered eating behaviors—but also broader domains essential for sustained recovery. These include improvements in psychological well-being, interpersonal functioning, emotional regulation, identity development, and overall quality of life, which are often profoundly affected by the disorder. Interventions targeting these broader outcomes should be designed to complement existing treatment frameworks and be feasibly integrated into established care pathways [14,15].

In particular, the consistent findings in the literature highlight two core neurocognitive difficulties commonly associated with AN: cognitive inflexibility—primarily manifested as weak set-shifting abilities [16]—and extreme attention to detail, often described as weak central coherence [17,18,19]. Cognitive flexibility refers to the ability to adjust and respond to evolving environmental requirements by flexibly switching between different rules, tasks, actions, and mental frameworks [20]. Consequently, impaired set-shifting or cognitive inflexibility leads to rigid or persistent thinking and behavior. Central coherence pertains to the ability to process information globally or holistically, whereas weak central coherence is reflected by an excessive focus on detail [21].

In individuals with AN, both impaired set-shifting and diminished central coherence commonly manifest through obsessive preoccupations related to food, body shape, and weight, as well as compulsive behaviors like calorie counting and excessive exercising. These cognitive aspects have been suggested to contribute to poor treatment engagement and response [22]. As a result, they have been included in the maintenance models of AN and targeted by specialized treatment approaches, such as cognitive remediation therapy (CRT) [23,24]. CRT was originally developed for people with brain injuries but has been adapted to help individuals with schizophrenia and, more recently, AN [25].

It is designed to be a brief intervention delivered as an adjunct to traditional interventions for AN [26], and it consists of cognitive exercises focused on the development of new thinking strategies and processes that are not directly related to emotions concerning eating and nutrition (i.e., weight and shape concerns or dietary restrictions).

CRT targets cognitive deficits by focusing on how individuals think rather than on the specific content of their thoughts. Increasing awareness of one’s habitual cognitive style enables the application of CRT exercises to modify maladaptive patterns of daily living—for instance, inflexible adherence to rigid routines that hinder social participation, repetitive checking behaviors that prolong task completion, or disproportionate time allocation to planning meals or exercise regimens at the expense of occupational, recreational, or interpersonal activities [27]. Preliminary research exploring the effectiveness of CRT in persons with AN showed that most find CRT acceptable and demonstrated the efficacy of CRT in improving cognitive flexibility, motivation to change, and better quality of life, with medium to large effect sizes in individuals with AN [28,29,30,31,32,33,34,35,36]. Still, how best to use CRT for the treatment of AN continues to be the subject of investigation.

When applied to individuals with schizophrenia and related disorders, CRT is frequently administered with the assistance of a computer-based platform, a type of treatment delivery referred to as computer-assisted cognitive remediation therapy (CA-CRT) [37,38,39,40]. It involves the completion by patients of a series of tasks on a computer while a trained facilitator engages them in a discussion about the tasks. Patients are encouraged to verbalize their process and to perform self-check-ins to gauge their performance.

The computer-assisted delivery format offers several theoretical and practical advantages in terms of psychological interventions, including improved scalability, potential for personalization of task difficulty and content, and enhanced patient engagement through interactive features. Moreover, digital platforms can facilitate remote delivery, making interventions more accessible to individuals who face geographic, mobility, or scheduling barriers. These benefits align with the growing interest in digital mental health tools as a complement or alternative to traditional face-to-face interventions [41,42,43].

While research on digital interventions for eating disorders remains limited, emerging findings suggest that computer- or internet-delivered programs may be effective in reducing core symptoms, improving motivation to change, and increasing access to treatment. However, most of the existing evidence focuses on guided self-help CBT for bulimia nervosa or binge eating disorder, and—to date—we are unaware of any research focused on testing digital adaptations of CRT for AN. The only study on the topic aimed at detecting changes in brain function potentially associated with CRT in AN [44], which led to encouraging results.

Therefore, the present multicenter randomized controlled trial (RCT) aims to implement and evaluate a personalized CA-CRT program for individuals with AN as an adjunct to standard nutritional rehabilitation (treatment as usual, TAU). The study will test the feasibility and efficacy of CA-CRT in enhancing selected neuropsychological outcomes (cognitive flexibility and central coherence) and psychological measures (eating disorder symptomatology, health-related quality of life, and motivation to change) among inpatients with AN. The feasibility of the study will be evaluated through indices such as the recruitment and retention rates and the patient outcomes. These metrics will help determine not only whether the intervention is acceptable but also whether it can be implemented in routine clinical settings. By delivering a structured, scalable, and individually tailored intervention, the trial seeks to promote more effective, patient-centered care approaches. It is hypothesized that participants allocated to the experimental group will demonstrate greater improvements in the targeted outcomes compared to those receiving standard care alone over the 5-week intervention period. Specifically, the primary hypothesis is that participants in the CA-CRT group will show significantly greater improvement from baseline to post-treatment than those in the TAU group in relation to cognitive flexibility, as measured by the Wisconsin Card Sorting Test (WCST), the Phonemic/Semantic Alternate Fluency Test, the Trail Making Test (TMT), the Test of Attentional Performance (TAP), the Detail and Flexibility Questionnaire (DFlex), and the Cognitive Flexibility Inventory (CFI). Improvements are also expected in the Central Coherence Index (CCI) of the Rey–Osterrieth Complex Figure (ROCF-C).

The secondary hypothesis is that the CA-CRT group will show greater reductions in their eating disorder symptoms (EDE-Q), as well as greater improvements in their quality of life (WHOQOL-BREF) and readiness to change (URICA), compared to those receiving TAU.

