### 2.3. Sample Size Calculation

The minimum sample size required for this study has been computed using an *a priori* sample size calculator (G*Power 3.1.9.2 software) for the *F* tests [46,47,48]. Participants will be randomly allocated into two groups: (A) TAU plus CA-CRT condition (experimental group) and (B) TAU-only condition (control group). Moreover, the recruits will be assessed before and after the intervention (i.e., 5 weeks). The Pillai V has been set *a priori* to take a value of 0.2, with an effect size of 0.5. Moreover, the type I error (*α*) rate has been set at 0.05 (two-sided), and the power (1 − *β*) at 0.95, respectively. The results showed that there is a 95% chance of correctly rejecting the null hypothesis of no significant interaction effect, with 54 recruits in total (27 per group) for each center.

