Moreover, the Standard Progressive Matrices (SPM) [54,55] will be administered. It consists of 60 items measuring nonverbal intelligence divided into 5 sheets (12 items each). Each item requires completion of a series of figures with a missing part that is presented among distractors, according to an increasing difficulty criterion.

Then, the Italian versions of the following neuropsychological tests will be collected pre- and post-treatment and used as the primary outcomes.

The Wisconsin Card Sorting Test (WCST) [56,57] will be used to assess abstract reasoning, mental flexibility, and problem-solving. The examinee has to match stimulus cards to one of four category cards. Cards can be matched by shape (cross, circle, triangle, star), color (red, blue, yellow, green), and number (one, two, three, four). The rule must be worked out by the feedback provided by the examiner (“right” or “wrong” response). When a rule is identified (i.e., 10 consecutive correct matches), the examiner changes the criterion without saying anything, and the examinee has to identify the new rule. Scoring provides the following indices: total mistakes, total correct responses, completed categories, perseverative mistakes, non-perseverative mistakes, percentages of perseverative mistakes, attempts to complete the first category, inability to retain the criterion, and task learning.

The Phonemic/Semantic Alternate Fluency Test [58] will be used to assess the verbal set-shifting ability. The examinee has to produce word pairs unusually, starting from a phonemic cue (letter A, F, S) and a semantic cue (color, animal, fruit), in 60 s. The raw score (number of word pairs obtained for each association (A–color; F–animal; S–fruit)) is adjusted for age, education, and gender; thus, it is converted into an equivalent score. Moreover, a composite shift index evaluating working memory is determined as follows: Total Alternate Fluencies/(Total Phonemic Fluencies + Total Semantic Fluencies/2).

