### 2.7. Statistical Analysis

Statistical analyses will be performed using SPSS version. 24.0 [73]. Descriptive analyses will be conducted on the experimental group and control group. After preliminary statistical assumption satisfaction, an independent samples T-test will be used to determine whether the groups differ in the psychodiagnostic measures administered at baseline. These potential differences will be used as covariates in the model. A multivariate analysis of covariance (MANCOVA) will then be conducted (factors: experimental group, control group, time; dependent variables: scores obtained in the neuropsychological and psychological measures; covariates: scores obtained in the psychodiagnostic measures at baseline). We will adopt this design because the dependent variables concerning the executive functions (WCST, alternate fluency, and TMT), as well as visuo-perceptive processing (ROCF-C), are moderately but significantly associated, given their involvement in frontal lobe abilities.

Partial eta-squared will be used to determine the effect size of the intervention. The analysis will be performed by an independent statistician, blinded to the treatment allocation, who will discuss the results with the researchers. Missing data will be handled using appropriate statistical methods to minimize bias and ensure robust results.

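### The Central Coherence Index is a primary outcome in section 2.5, belongs to neither labelled hypothesis in section 1, and enters section 2.7 only within one joint MANCOVA under another construct name, so no stated test supports a central-coherence claim

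*Protocol article*

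**What the plan says.** All places are in the protocol article.

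- **Abstract.** The conclusion rests on two targets: "By specifically targeting cognitive inflexibility and poor central coherence in a scalable, individualized format".
- **Section 1 (hypotheses).** The aims name cognitive flexibility and central coherence as the neuropsychological outcomes. The primary hypothesis is about flexibility and lists six instruments (WCST, alternate fluency, TMT, TAP, DFlex, CFI). The secondary hypothesis lists EDE-Q, WHOQOL-BREF and URICA. Between the two stands "Improvements are also expected in the Central Coherence Index (CCI", with no tier attached.
- **Section 2.5.** The Rey figure and its CCI fall in the block introduced by "neuropsychological tests will be collected pre- and post-treatment and used as the primary outcomes".
- **Section 2.7.** One MANCOVA takes all neuropsychological and psychological scores as dependent variables. The reason given is that the executive scores, "as well as visuo-perceptive processing (ROCF-C), are moderately but significantly associated". Neither the CCI nor central coherence is named in this section.
- **Section 3.** Gains are expected in visuospatial processing; central coherence is again not named.

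**The concern.** The same score has two roles. If the CCI shows no difference between arms, a primary outcome has failed under section 2.5, while the primary hypothesis as worded in section 1 is untouched. A statistical analysis plan cannot settle this while the protocol says both.

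The only analysis that section 2.7 fixes is a joint one. A joint test asks whether the arms differ on any combination of the scores and does not say which score moved. The Abstract nevertheless draws a conclusion about both targets. A positive result produced by flexibility alone could therefore be reported under a heading that includes central coherence, and the CCI's standing could be raised or lowered once results are known.

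The construct names add to this. The Rey figure measures central coherence in sections 1 and 2.5 and visuo-perceptive processing in section 2.7. The DFlex has an attention-to-detail subscale, and section 1 describes extreme attention to detail as weak central coherence. Yet the primary hypothesis counts the whole DFlex as a flexibility measure.

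**Working it through.** **1. The plan's own sample size.** Inputs from section 2.3: "The Pillai V has been set *a priori* to take a value of 0.2, with an effect size of 0.5"; "the type I error (*α*) rate has been set at 0.05 (two-sided"; power 0.95; "with 54 recruits in total (27 per group) for each center".

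- f² = V/(1 − V) = 0.2/0.8 = 0.25, so f = 0.5, as stated.
- For a group-by-time interaction with two groups, two time points and one dependent variable: λ = 0.25 × N, with 1 and N − 2 degrees of freedom.
- N = 54: λ = 13.5, power 0.9501. N = 53: power 0.9464.

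The stated 54 is reproduced, but with a single dependent variable. With seven scores tested jointly at the same V, power at N = 54 is about 0.69. The sample size therefore already fits a stand-alone test of one outcome such as the CCI: at V = 0.2 and alpha 0.025, power is 0.910 at N = 54 and above 0.999 at N = 162.

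**2. Does a significant joint result speak to the CCI?** Inputs: 3 centers × 54 = 162 patients, 81 per arm. Assumptions: effects in SD of the change score, seven scores (six flexibility, one CCI), equal correlation ρ between scores, alpha 0.05.

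Two-group Hotelling T² with p scores:
- λ = (81/2) × Q
- Q = [Σd² − ρ(Σd)²/(1 + (p − 1)ρ)]/(1 − ρ)
- degrees of freedom p and 161 − p, here 7 and 154

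With d = 0.4 on six scores and 0 on the CCI, Σd² = 0.96 and (Σd)² = 5.76.

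| ρ | Q | λ | Joint test significant |
|---|---|---|---|
| 0 | 0.960 | 38.9 | about 99.9% |
| 0.3 | (0.96 − 1.728/2.8)/0.7 = 0.490 | 19.8 | 91% |
| 0.5 | (0.96 − 2.88/4)/0.5 = 0.480 | 19.4 | 91% |

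The joint test nearly always rejects although the CCI effect is zero.

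**3. Power when only the CCI moves, by 0.5 SD.** Σd² = (Σd)² = 0.25.

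- Own test, 1 and 160 degrees of freedom, λ = 40.5 × 0.25 = 10.125: 88.5% at alpha 0.05 and 82.0% at alpha 0.025.
- Joint tests at alpha 0.05:

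| ρ | 7 scores | 20 scores |
|---|---|---|
| 0 | 60% | 36% |
| 0.3 | 72% | 51% |
| 0.5 | 87% | 70% |

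At ρ = 0.6 the seven-score test reaches 94% (Q = (0.25 − 0.15/4.6)/0.4 = 0.543, λ = 22.0). Whether the joint test is weaker for the CCI thus depends on the correlation and on the number of scores.

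**The case against.** Several stronger readings are tempting, and the document does not support them.

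- *The trial cannot say whether central coherence improved.* It can. The Rey figure is a named dependent variable, measured in both arms before and after treatment, so a CCI contrast and its partial eta-squared can be estimated. Follow-up tests per outcome are commonly left to an analysis plan, which is not shown.
- *The CCI lies outside every hypothesis.* Only the two labelled ones omit it. The general hypothesis in section 1 expects greater improvement in the targeted outcomes, and central coherence is a named target. No section calls the CCI secondary or exploratory.
- *The CCI is the only measure of this target.* The DFlex attention-to-detail subscale plausibly bears on it too.
- *The CCI is singled out by having no test of its own.* No outcome has a separately stated test.
- *Pooling dilutes a CCI effect.* This is not certain. At a correlation of 0.5 the joint seven-score test (87%) beats the single test at alpha 0.025 (82.0%), and at 0.6 (94%) it beats the unadjusted single test (88.5%). Section 2.7 itself calls the scores moderately associated.

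It is also fair to say that rejecting the joint null when six of seven effects are real is a correct rejection. The 91% to 99.9% shows only that the joint test does not locate the effect.

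What stands is the conflict over tier between sections 1 and 2.5, the change of construct name in section 2.7, and a single joint test that cannot by itself carry a separate central-coherence claim.

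**Conclusion.** The concern holds as a conflict of role and a gap in what the stated test can support. The CCI is primary in section 2.5 and in neither labelled hypothesis in section 1, and section 2.7 fixes only a joint test under another name. A significant MANCOVA would not show that central coherence improved: with a flexibility-only effect of 0.4 SD and 81 patients per arm, the joint seven-score test is significant in about 91% to 99.9% of trials.

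That range rests on assumed effects, equal correlations from 0 to 0.5, seven scores and full data on 162 patients. The planned MANCOVA holds more scores than seven, since it adds the psychological measures and several tests yield more than one index. The conflict between the sections does not depend on any of these assumptions.

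**What to change.** 1. Give the CCI one tier in sections 1, 2.5 and 2.7. Since section 2.5 already calls it primary, the consistent choice is a second primary hypothesis on central coherence.
2. Name a separate between-arm test of the CCI at week 5, with multiplicity controlled against the flexibility test, for example by Holm.
3. State that any claim about central coherence rests on that test and not on the joint MANCOVA.
4. Use the term central coherence throughout, including sections 2.7 and 3.
5. Say whether the DFlex attention-to-detail subscale belongs to flexibility or to central coherence.

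The cost is wording in a few sections and one extra test. Under Holm the CCI is tested at 0.025 at worst, which puts power for a 0.5 SD effect at 82.0% instead of 88.5% with 162 patients; if the flexibility test is significant, the CCI is tested at the full 0.05. The change should be made before results by arm are seen.

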## 2. Materials and Methods

The study will be conducted as a multicenter randomized controlled trial across three specialized Italian facilities dedicated to the nutritional rehabilitation and treatment of those with eating and weight disorders: IRCCS Istituto Auxologico Italiano in Piancavallo Oggebbio (VB), Beato Palazzolo Hospital in Bergamo, and the Mariconda Regional Eating Disorders Unit in Salerno.

Participants who meet the inclusion criteria will be enrolled on a rolling basis and randomized in a 1:1 ratio into two groups using a secure, computerized, web-based system. The experimental group will receive the CA-CRT intervention in addition to the standard rehabilitation program (treatment as usual, TAU), while the control group will follow TAU alone.

In line with national guidelines, the standard TAU protocol will be applied consistently across all the participating sites [45].

The study was registered on ClinicalTrials.gov NCT05912036 (https://clinicaltrials.gov/study/NCT05912036) on 20 June 2023 and follows the SPIRIT Statement for reporting a randomized trial protocol. The corresponding SPIRIT checklist is included as a supplementary document (see Supplementary Table S1).

